### Sample size

Pilot data collected from 31 participants residing in a single-site aged care facility were used to guide power calculations for this study ([name], [name], [name], [name]: Vision Optimisation in Residential Care: A pilot study, unpublished, 2011). They showed that following correction, 30% of participants had improved distance vision by at least two lines and 30% of the participants improved by ≥ 0.2 Log units on a text reading chart for near vision. Therefore, the sample size calculation is based on achieving a 30% improvement in VA (near and distance vision) at two- and six-month follow-up visits in the intervention group compared to controls. The anticipated effect size will be ~ 0.65 based on our pilot work. At a significance level of 0.05, with 38 participants in each arm (overall total of 76 participants) we will have 80% power to detect a group difference. We assume an intra-cluster correlation coefficient (ICC) within-facility of 0.05 which corresponds to the levels found in similar work in nursing homes [28]. The inflation factor (or design effect) will be estimated using the following formula: Inflation factor = 1+ (number of patients per facility [50]-1) X ICC = 3.5. To take cluster design into account, we need a total sample size of 266 [76 × 3.5]. However, to adjust for non-compliance with the intervention (~ 10% due to people who seek vision care on their own in the usual care arm, or people who refuse the intervention in the intervention arm) and loss to follow-up (~ 25% largely due to deaths), the effective sample size needs to be increased by a factor of 1.48 (1/0.90 × 1/0.75) resulting in an initial enrolment requirement of 395 individuals.

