**Methods/design:**

This protocol describes a multicentered, prospective, randomized controlled trial. A total of 395 participants with distance vision < 6/12 (0.30 LogMAR) and/or near vision N8 (1.00 M) or worse will be recruited from 38 urban and rural aged care facilities across Victoria, Australia. Aged care facilities will be randomized (1:1) to one of two parallel groups. Participants in the ROC group will receive a comprehensive and tailored eye care pathway that includes, as necessary, refraction and spectacle provision, cataract surgery, low vision rehabilitation, and/or a referral to an ophthalmologist for funded treatment. Usual care participants will be referred for an evaluation to the eye care service associated with the facility or an eye care provider of their choice. The primary outcome will be presenting near and distance vision assessed at the two- and six-month follow-up visits, post baseline. Secondary outcomes will include vision-specific quality of life, mobility, falls, depression, and eye care utilization at two and six months. An incremental cost-effectiveness analysis will also be undertaken.

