### Settings and study participants

Prospective participants will be recruited from 38 aged care facilities in urban and rural Victoria, Australia. Before enrolment or study assessments being performed, prospective participants will be asked to sign a written consent form. Residential care staff will identify participants who are cognitively able to give informed consent. Participants who consent to participate in the study will be screened for study eligibility by a research assistant.

The inclusion criteria are:Presenting distance < 6/12 (0.30; Logarithm of the Minimum Angle of Resolution-LogMAR) and/or near vision ≤ N8 (1.00 M) assessed uniocularly and binocularly using the Bailey-Lovie LogMAR [16] charts;Able to speak English;Moderate cognitive functioning or better as assessed by the Psychogeriatric Assessment Scale (PAS) [17] (score ≤ 15);Ability to undergo VA testing and provide reliable results.

The exclusion criteria are:Residents in respite care (short-term stay);Severe cognitive impairment (score of ≥ 16 on the PAS);Non-English speaking;Inability to be tested for vision;Contraindication(s) as indicated by the general practitioner responsible for the resident’s care.

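### The design effect assumes 50 patients per facility, but 395 participants in 38 facilities is about 10 each, so the stated 80% power at an effect size of 0.65 does not describe this trial

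*Protocol article*

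**What the plan says.** The Sample size section of the protocol article starts from a standardised effect: "The anticipated effect size will be ~ 0.65 based on our pilot work". It continues: "At a significance level of 0.05, with 38 participants in each arm (overall total of 76 participants"), for which it claims 80% power. With an assumed within-facility ICC of 0.05 it then applies "Inflation factor = 1+ (number of patients per facility [50]-1) X ICC = 3.5", which takes 76 to 266. For about 10% non-compliance and about 25% loss to follow-up, "the effective sample size needs to be increased by a factor of 1.48 (1/0.90 × 1/0.75"), which gives 395 to enrol.

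The Abstract (Methods/design) repeats the total: "A total of 395 participants with distance vision < 6/12". It also says: "Aged care facilities will be randomized (1:1) to one of two parallel groups". Settings and study participants gives the number of clusters: "Prospective participants will be recruited from 38 aged care facilities in urban and rural Victoria, Australia". Randomization confirms that everyone in a facility is in the same arm. Statistical analysis plans intention-to-treat, with a random intercept for within-cluster correlation.

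**The concern.** The cluster size in a design effect is the number of participants analysed per randomised unit. The figures 50 per facility, 395 participants and 38 facilities cannot all be true of participants: 395/50 is about 8 facilities, and 38 × 50 is 1,900 people. The article gives no reason for the 50.

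What is at stake is how the trial is described. The article tells readers that the trial has 80% power for an effect of 0.65. A reader would conclude that an effect of 0.4 SD is out of reach, when on the protocol's own ICC it is about the size the trial can detect with 80% power.

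The same chain has a second fault. The section describes non-compliers as usual-care residents who find eye care themselves, or intervention residents who refuse it. Under intention-to-treat these people remain in the analysis and shrink the difference between arms. Dividing by 0.90, as if they were lost, understates the inflation needed.

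**Working it through.** **Inputs from the article.** Effect 0.65, alpha 0.05 (taken as two-sided, which reproduces 38 per arm), power 80%, ICC 0.05, 50 per facility, non-compliance 10%, loss 25%, enrolment 395, 38 facilities, 1:1 by facility.

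**Inputs assumed here.** Cluster-size CV of 0.6 to 0.8 for the unequal-size case. The article gives none.

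**1. The stated chain reproduces.**
- n per arm = 2(1.960 + 0.842)²/0.65² = 37.2, rounded up to 38; total 76.
- Design effect = 1 + (50 − 1) × 0.05 = 3.45, stated as 3.5.
- 76 × 3.5 = 266.
- 266/(0.90 × 0.75) = 394.1, rounded up to 395.

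The multiplication is sound. The fault lies in the input of 50.

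**2. Design effect for 38 facilities**, using 1 + (m − 1) × 0.05:

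| Basis | m | Design effect |
|---|---|---|
| 266/38 | 7.0 | 1.30 |
| 395 × 0.75 = 296; 296/38 | 7.8 | 1.34 |
| 395/38 | 10.4 | 1.47 |

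With unequal clusters, 1 + [(1 + CV²)m − 1] × 0.05 at m = 7.8 gives 1.48 (CV 0.6) and 1.59 (CV 0.8).

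**3. Dilution from non-compliance under intention-to-treat.**
- If 10% is the net dilution: 0.90 × 0.65 = 0.585, and the inflation factor is 1/0.90² = 1.23.
- If it is 10% in each arm: the difference shrinks by 1 − 0.10 − 0.10 = 0.80, so d = 0.52 and the factor is 1/0.80² = 1.56.
- The article uses 1/0.90 = 1.11.

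**4. Power with 296 analysed.** Effective N = 296/design effect. Noncentrality = d × √(effective N/4), referred to a t distribution with 38 − 2 = 36 degrees of freedom.

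| Cluster sizes | Effective N | Power at 0.65 | Power at 0.585 | Power at 0.52 | Detectable d at 80% |
|---|---|---|---|---|---|
| Equal | 221 | 99.7% | 98.8% | 96.4% | 0.39 |
| CV 0.6 | 200 | 99.4% | 98.1% | 94.7% | 0.41 |
| CV 0.8 | 186 | 99.1% | 97.3% | 93.2% | 0.42 |

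**5. Sensitivity to the ICC.** With equal clusters and 296 analysed, an assumed ICC of 0.10 gives 98.7% power at 0.65, and 0.20 gives 94.3%.

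**The case against.** The strongest defence is that the error is harmless. It makes the trial larger than its stated target needs, and no participant, estimate or type I error rate suffers. The planned random-intercept model uses the actual cluster sizes whatever the sample size section says. Trial status has recruitment ending by 1 December 2018, and the article appeared on 26 November 2018, so a recalculation changes text and not the trial. A null result would in any case be read mainly from its confidence interval. All of this stands, and it makes the point a correction to a stated figure rather than a threat to the trial.

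It might also be said that 50 is the number of residents per facility. The article does not say so, and it would not help, because clustering inflates variance through those analysed, not those living there.

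On non-compliance, the article does not say whether the 10% is overall or per arm, so neither 1.23 nor 1.56 can be called the right factor. What stands is that 1/0.90 is too small on either reading. The planned per-protocol repeat does not change this: it is defined by completing the trial, not by taking up the intervention.

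Two stronger readings are tempting and fail:
- A reader might multiply 76 by 1.30 to 1.47 and infer that roughly 100 to 110 analysed participants would be enough. That cuts N while keeping 7 to 10 per facility. In 38 facilities, 100 to 110 people is fewer than 3 each. Solving N = 76 × [1 + (N/38 − 1) × 0.05] gives about 80, which describes a different trial.
- A reader might accept 3.5 and infer that the non-compliance slip leaves the trial short of 80% power. Clusters of 50 would leave 296 analysed in about 6 facilities, which contradicts the 38. No such shortfall follows for the design described.

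**Conclusion.** The point holds as an inconsistent input. For 395 participants in 38 facilities the design effect is about 1.3 to 1.5, or up to about 1.6 under the assumed size variation at the analysed number, against the stated 3.5. Power at 0.65 is above 99%, not 80%, and the detectable effect is about 0.39 to 0.42. The non-compliance step errs in the opposite direction but is outweighed: power at the diluted effect stays between about 93% and 99%.

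These figures rest on the article's ICC of 0.05 and 25% loss, a two-sided test, and facility-level degrees of freedom. The unequal-cluster figures also rest on the assumed CV. The documents do not support calling the trial under-powered, and they give no reason to change enrolment or the analysis.

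**What to change.** Keep enrolment at 395. In the Sample size section:

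- Replace 50 with the expected number of analysed participants per facility (about 8), add an allowance for unequal sizes, and restate the design effect.
- Say whether the 10% non-compliance is a net figure or applies to each arm. Treat it as dilution of the effect under intention-to-treat, and keep 1/0.75 for loss to follow-up only.
- Restate power at 0.65 and at the diluted effect, and give the detectable difference (about 0.4 SD) for 38 facilities.
- If 50 participants per facility is really intended, reconcile that with the 38 facilities given in the Abstract and in Settings and study participants.

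The cost is one recalculation and a few sentences. It needs no extra participants and no change to the analysis.

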### Statistical analysis

The primary and secondary outcomes will be assessed using an intention-to-treat analysis applied to individual participants and repeated using the per-protocol sample (only participants who complete the clinical trial including the second assessment). To compare the effectiveness of ROC with usual care, presenting and best corrected near and distance VA (primary outcome) at the two- and six-month follow-ups will be analyzed and the differences from baseline VA will be used to investigate changes. The near and distance VA change is expected to be normally distributed and analysis of covariance will be used to compare the difference, adjusting for baseline values. Effect sizes for both groups will be calculated using Cohen’s d coefficient [27]. To determine the effectiveness of ROC on secondary outcomes, a Multivariable General Linear Model will be used to compare differences at two and six months from baseline on the IVI-RC, EQ-5D-3L and CSDD. If the EQ-5D-3L data are skewed, a multivariable quantile regression model will be used. Falls data will be compared across intervention and usual care groups at six months using a negative binomial regression if the data are over-dispersed. Changes in mobility will be analyzed using Mann–Whitney U tests. The difference in utilization of distance and near vision glasses and low vision aids between the treatment groups will be compared using the Chi-squared test and the utilization time will be compared using Student’s t-test or non-parametric test if appropriate. A multi-level model with a random intercept parameter will be utilized to account for within cluster correlations. All analyses will be performed using STATA version 15 (StataCorp. 2017. Stata Statistical Software: Release 15. StataCorp LLC, College Station, TX, USA).

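### The sample size treats the 10% non-compliers as drop-outs, although the intention-to-treat analysis keeps them, so the 1/0.90 term should be a diluted-effect term 1/f²

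*Protocol article*

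**What the plan says.** The Sample size section of the protocol article starts from a standardised effect ("The anticipated effect size will be ~ 0.65 based on our pilot work"). With 38 participants per arm, 76 in all, it states that "we will have 80% power to detect a group difference". It multiplies 76 by a design effect of 3.5, based on 50 residents per facility and an ICC of 0.05, to reach 266. It then says that "the effective sample size needs to be increased by a factor of 1.48", made up of 1/0.90 for non-compliance and 1/0.75 for loss to follow-up, and arrives at 395.

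The non-compliers are defined as "people who seek vision care on their own in the usual care arm, or people who refuse the intervention in the intervention arm". The section does not say whether the figure of about 10% applies in each arm or is the total over both.

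The Statistical analysis section states: "The primary and secondary outcomes will be assessed using an intention-to-treat analysis applied to individual participants". The analysis is repeated on a per-protocol set that is defined only by completing the trial, including the second assessment. The Retention and withdrawal section aims to follow everyone who does not expressly withdraw. Its grounds for withdrawal are loss to follow-up, withdrawn consent and death. Declining ROC or obtaining eye care elsewhere is not among them.

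**The concern.** Dividing by one minus a rate replaces people whose outcome is missing. It is the right form for the 25% lost. The 10% are a different group: their visual acuity is measured and they are analysed in the arm to which their facility was randomized. The per-protocol repeat does not remove them either, because a refuser or a switcher can complete follow-up. No stated analysis drops them, and nothing in the section lowers the effect of 0.65 on their account.

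Keeping them does not reduce the number analysed. It reduces the difference that the analysis can expect to see, and the required number rises with the inverse square of that difference. At stake is whether the stated factor, and the power attached to 395, describe the planned analysis.

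**Working it through.** **Inputs from the Sample size section:** alpha 0.05 (sidedness not stated; two-sided assumed, because two-sided gives the stated 38 per arm while one-sided gives 30), power 80%, effect 0.65, ICC 0.05, 50 per facility, non-compliance 10%, loss 25%. **From the abstract and the Settings section:** 1:1 allocation of facilities, 395 participants, 38 facilities.

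**1. The plan's own figure.**
- Two-sample comparison at d = 0.65: 38 per arm, 76 in total.
- Design effect: 1 + (50 − 1) × 0.05 = 3.45, rounded in the plan to 3.5. Then 76 × 3.5 = 266.
- 266 / (0.90 × 0.75) = 394.1, which rounds up to 395. The stated figure reproduces.

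**2. Dilution under intention to treat.** Let r be the refusal rate in the ROC arm, c the rate of outside care in the usual care arm, and Δ the full effect. If refusers gain nothing and switchers gain all of Δ, the expected difference is (1 − r)Δ − cΔ = fΔ, with f = 1 − (r + c). The requirement scales with 1/f².
- 10% is the sum over both arms: f = 0.90 and 1/f² = 1.235, against 1/0.90 = 1.111 in the plan. With loss, 1/(0.81 × 0.75) = 1.65.
- 10% in each arm: f = 0.80 and 1/f² = 1.5625. With loss, 1/(0.64 × 0.75) = 2.08.
- If switchers gain only part of the effect, 10% in each arm gives f between 0.80 and 0.90.

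**3. Consequence on the section's own design effect (3.5).** Required enrolment is 266 / (0.81 × 0.75) = 437.9, so 438, or 266 / (0.64 × 0.75) = 554.2, so 555. With 395 enrolled, 395 × 0.75 = 296 remain, and 296.25 / 3.5 / 2 = 42.3 effective per arm. Two-sample t-test power:

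| f | Diluted effect | Power |
|---|---|---|
| 1 | 0.65 | 84.0% |
| 0.90 | 0.585 | 75.8% |
| 0.80 | 0.52 | 65.7% |

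**4. Consequence with the cluster size implied by the design.** 395 / 38 = 10.4 per facility. The design effect is 1 + (10.4 − 1) × 0.05 = 1.47, assuming equal cluster sizes. Effective number per arm: 296.25 / 1.47 / 2 = 100.8.

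| f | Power | Enrolment needed for 80% (76 × 1.47 / f² / 0.75) |
|---|---|---|
| 0.90 | 98.5% | 184 |
| 0.80 | 95.7% | 233 |

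Both requirements lie below 395.

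**The case against.** The strongest reply is that the consequence disappears in the trial as described. The figures of 76% and 66% need 50 participants per facility. In 38 facilities that would be 38 × 50 = 1,900 people, not 395. The cluster-size input errs in the opposite direction and by more, so 395 keeps ample power after dilution. This stands, and it rules out a reading that a reader might draw from the wrong factor: that the trial is underpowered or must enrol more. The documents do not support that reading.

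Second, the inputs are approximate and the benchmark is an unadjusted t-test, while the plan adjusts for baseline. If 0.65 is an unadjusted standardised difference (the article does not say), an assumed baseline–outcome correlation of 0.3 would lift 75.8% to 79.6%, and 0.4 would lift it to 82.7%. Those correlations are assumptions, not figures from the document. This part stands as a caution: at f = 0.90 the deficit on the section's chain is small.

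Third, 1/0.90 would be nearly right if non-compliers lost only about half the contrast: with the two rates summing to 10%, f = 0.95 and 1/0.95² = 1.108. The section makes no such argument. It uses the same form as for loss to follow-up, so this does not rescue the term as written.

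Finally, the stated multiplication is correct. The error is in the choice of method, not in the arithmetic.

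**Conclusion.** The point holds as a point of method. The 1/0.90 term conflicts with the protocol's own follow-up and analysis rules, and the factor 1.48 is wrong for an intention-to-treat comparison. The corrected combined factor is 1.65 (f = 0.90) or 2.08 (f = 0.80). The text does not settle which, because it does not define the 10%.

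Within the section's own calculation, 395 would give about 76% or 66% power, and about 438 or 555 would be needed. These figures are conditional on the design effect of 3.5 and are not the power of this trial. With 10.4 residents per facility, power is about 98% or 96%. All of this assumes a two-sided test, equal cluster sizes, an ICC of 0.05, an undiluted effect of 0.65, no benefit to refusers and full benefit to switchers.

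It is still worth correcting. An opposite error elsewhere does not make 1/0.90 right, and a recalculation that mended only the cluster size would carry this term forward.

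**What to change.** In the Sample size section:
- Replace the 1/0.90 term by a diluted effect, f × 0.65, or equivalently by 1/f². Keep 1/0.75 for loss to follow-up.
- State whether the 10% is the rate in each arm or the sum over both, and what benefit switchers are assumed to gain.
- State that non-compliers remain in the intention-to-treat analysis and dilute the effect.
- Keep 395 enrolled, and restate its power in a single recalculation that also uses the cluster size actually planned. Do not report 76% as the trial's power, and do not fix 1.65 as the factor until the 10% has been defined.

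The cost is a few lines of text and one recalculation. No participants are added, and neither the design nor the analysis changes.

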### Missing data

The differences between the intervention and usual care groups in the proportion and reason of participant withdrawal will be compared using the Chi-squared test. The multiple imputations method using chained equations (MICE) will be used to handle missing data.

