#### Person-centered outcomes (secondary)

Mobility will be assessed using the Aged Care Funding Instrument (ACFI) [20] module 2 developed by the Department of Health and Ageing. This component of the ACFI relates to the participant’s usual day-to-day assessed care needs with regard to mobility. Mean mobility scores will be compared between groups. ACFI data will be collected regularly by residential care facility staff.

Vision-specific QoL will be measured using the Impact of Vision Impairment for Residential Care (IVI-RC). The IVI-RC is a 28-item questionnaire developed to measure the impact of vision impairment on activity limitation and emotional wellbeing, and has been adapted specifically to the aged care setting by the study team from the original 28-item IVI questionnaire [21, 22].

Depressive symptoms will be determined using the Cornell Scale for Depression in Dementia (CSDD) [23]. This measure was chosen due to its suitability for use with individuals with moderate cognitive functioning. The interviews focus on depressive symptoms and signs occurring during the week before the interview. The final ratings of the CSDD represent the rater’s clinical impression. Each item is rated for severity on a scale of 0–2 (0 = absent, 1 = mild or intermittent, 2 = severe). The item scores are added together. Scores of 0–8, 9–13, 14–18, and 19–38 indicate no or minimal, mild, moderate, and major depressive symptoms [24].

Regarding falls rate, residential care settings have an incident reporting system (which varies from paper based to computerized systems) where any incident including falls will be recorded. Falls data will be retrieved from incident reporting systems in the participating residential care facilities and the proportion of falls will be compared between groups.

Health-related QoL will be assessed using the five-dimension EuroQoL (EQ-5D-3L) [25], a descriptive system that covers five dimensions (Mobility, Self-care, Usual Activities, Pain/Discomfort, and Anxiety/Depression). The EQ-5D-3L raw data can be converted to utilities, which will be used for our economic analyses.

With regard to utilization of visual devices (distance and near vision glasses; low vision aids), at the two- and six-month follow-up visits, participants in the intervention arm who have been prescribed spectacles or low vision aids, will be asked to self-report on how often the device has been used during the week, for how long it was used, and for what tasks.

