### Retention and withdrawal

We will seek to follow up all participants except those who expressly withdraw from the study. Withdrawal at the participant level will be considered if any of the following occurs: participant is lost to follow-up; withdrawal of consent; or death. All withdrawals will be recorded and the reason will be specified.

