### Cost-effectiveness analysis

We will perform an incremental cost-effectiveness analysis from the payer perspective. Direct intervention costs (labor, material and supplies, and contracted services costs) associated with delivering the intervention over the one-year period will be collected and follow a cost collection approach described elsewhere [29]. The incremental costs of the intervention will need to account for any vision services received by the usual care group and any differences in costs for non-vision related services that may be an indirect result of the intervention. Information will be collected for any participants who fall or are hospitalized, transferred to high care or die. Aggregating these costs over the six-month period and adding them to the direct costs of the ROC intervention group, will allow the total medical costs for the intervention and the usual group to be quantified. The incremental cost-effectiveness ratio (ICER) will be calculated using the estimated mean difference in effect (EQ-5D-3L) and the estimated mean difference in costs between the intervention and the control groups. The ICER indicates the average incremental cost to gain one additional quality-adjusted life year (QALY). Cost data are likely to be skewed. Therefore, using non-parametric bootstrapping, 1000 replicates [30] will be generated to estimate the 95% confidence intervals around the ICER. A cost-effectiveness acceptability curve (CEAC) [31] will be used to show the probability that the intervention is cost-effective for a range of monetary values that a decision maker might be willing to pay for a unit change in QALYs. Cost-effectiveness will initially be quantified assuming that QALYs are only sustained for one year, but an assessment will also be made based on the assumption that they continue to accrue each year for the expected remaining life years in the study sample. Additional one-way (and n-way) deterministic sensitivity analyses will be performed to examine the effect of changing one (or n) of the model parameters.

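### Deaths are expected to make up most of a 25% loss to follow-up, yet the stated remedy for missing data is MICE with no exception for residents who have died

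*Protocol article*

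**What the plan says.** All references are to the protocol article.

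- **Sample size** plans for "loss to follow-up (~ 25% largely due to deaths") and inflates enrolment to 395 partly for that reason.
- **Retention and withdrawal** lists the events that count as withdrawal: "participant is lost to follow-up; withdrawal of consent; or death". The reason for each withdrawal is to be recorded.
- **Statistical analysis** specifies an "intention-to-treat analysis applied to individual participants and repeated using the per-protocol sample", where the latter sample is "only participants who complete the clinical trial including the second assessment". The primary analysis concerns "presenting and best corrected near and distance VA (primary outcome) at the two- and six-month follow-ups".
- **Missing data** compares the proportion of and reasons for withdrawal between groups, then states: "The multiple imputations method using chained equations (MICE) will be used to handle missing data". No other method is named and no category of participant is set apart.
- **Cost-effectiveness analysis** builds the ICER on the "estimated mean difference in effect (EQ-5D-3L") and reads it as cost per QALY. Information on residents who die is collected for costing, but no utility after death is given.
- **Falls** are described in three ways: as a rate in the objectives, under Person-centered outcomes as "the proportion of falls will be compared between groups", and in Statistical analysis by a negative binomial model if the data are over-dispersed.

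**The concern.** Multiple imputation estimates a value that exists but was not observed. A resident who dies before the six-month visit has no six-month acuity, IVI-RC or CSDD score. An imputation model fitted to survivors would supply one anyway, and the resulting treatment effect would describe a population in which nobody dies. That is a serious departure in a trial that expects deaths to be the main cause of loss.

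For EQ-5D the problem differs. A value after death does exist by convention, namely 0, and a survivor-based prediction would replace it with a positive utility. What is at stake is the meaning of the acuity and quality-of-life comparisons and the size of the QALY difference in the ICER.

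**Working it through.** 1. **The plan's own figure.** Inputs from Sample size: effect size 0.65, significance level 0.05 (taken as two-sided), power 80%. The normal approximation gives 38 per arm, so 76 in total. Then 76 × 3.5 = 266, and 266 / (0.90 × 0.75) = 394.1, against 395 stated. The figure reproduces.

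2. **Expected losses.** 0.25 × 395 = 98.75, about 99 residents.

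3. **How many are deaths.** The share is not quantified, so it is assumed:
   - 50%: about 49 residents (12.5% of those enrolled)
   - 75%: about 74
   - 90%: about 89
   - 100%: about 99 (25% of those enrolled)

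4. **Six-month utility difference, equal mortality.** Let Δ be the difference among survivors and d the proportion dead in each arm. With utility 0 after death the difference over all randomised residents is (1 − d)Δ. If the dead receive values that carry the survivors' effect, it is Δ. The overstatement factor is 1/(1 − d):
   - d = 0.125: 1/0.875 = 1.14, or 14% too large
   - d = 0.25: 1/0.75 = 1.33, or 33% too large

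5. **Six-month utility difference, unequal mortality.** If the mean imputed utility u is the same in both arms, the error in the difference is u × (difference in mortality). With assumed u of 0.4 to 0.7 and an assumed mortality difference of 2 to 5 percentage points, it runs from 0.4 × 0.02 = 0.008 to 0.7 × 0.05 = 0.035. This is survival information that the ICER would lose.

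6. **QALYs over six months.** The proportional error is smaller here, because those who die contribute while alive. As an assumed illustration, a utility difference of 0.05 reached linearly by month 2 and held to month 6 gives 0.05 × (2/12)/2 + 0.05 × 4/12 = 0.0042 + 0.0167 = 0.0208 QALY. If 20% die in each arm with three months (0.25 year) remaining, the excess in the between-arm contrast is 0.20 × 0.25 × 0.05 = 0.0025 QALY, or 12% of 0.0208.

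7. **Does the repeat analysis help?** The completer sample leaves out everyone who died, so it conditions on survival. It also drops living residents who missed the visit. It cannot inform a QALY analysis in which deaths must count.

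**The case against.** The strongest reply is that the Missing data section is two sentences in a condensed article. It does not say that values after death count as missing, and a statistical analysis plan not shown may restrict MICE to the living. That stands as a limit on certainty: the article does not state outright that the dead will be imputed. It does not remove the point. The article is not silent; it names one method, classes death with the other withdrawals, and predicts that deaths will dominate.

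Several stronger readings are tempting but unsupported:

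- **That every missing value will be imputed, by a model ignoring facility.** The text says neither. No imputation model is given, and chained equations can include facility.
- **That the QALY error exceeds the treatment gain.** Crediting 20% of residents with utility 0.5 for a quarter of a year adds 0.20 × 0.25 × 0.5 = 0.025 QALY per participant in each arm, more than 0.0208. With equal mortality that credit cancels from the contrast, leaving the 0.0025 shown above.
- **That a mortality difference would go unseen.** The comparison of withdrawal proportions and reasons between groups would largely show it. It would still not enter the ICER.
- **That the per-protocol sample keeps every non-complier.** Those who do not complete are excluded. The fault is the label.
- **That early deaths will be counted as low fallers.** The article names a falls rate and a count model; whether time at risk enters is not stated.
- **That dates of death are already collected.** Only the reason for withdrawal and unspecified information on deaths are mentioned.

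Baseline-adjusted analysis of covariance with a random intercept is acceptable, so there is no case for requiring a different primary model.

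**Conclusion.** The point holds as a fault in the wording of the plan. Followed as written, it would impute acuity, questionnaire scores and utilities for residents who have died: roughly 49 to 99 of 395 if half to all of the expected losses are deaths.

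For acuity, IVI-RC and CSDD the consequence is an ill-defined comparison whose numerical effect cannot be computed from the article. For the six-month utility difference the overstatement is about 14% to 33%, assuming equal mortality, utility 0 after death and a survivor effect carried over to the dead. For six-month QALYs it is about 12% in the single illustration above. Neither mortality by arm nor utilities are given, so these are ranges under stated assumptions and not predictions. The sample size of 395 is unaffected.

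**What to change.** - **Missing data:** state that MICE applies only to residents alive at the scheduled visit, with facility and arm in the imputation model, in line with the random-intercept analysis.
- **Statistical analysis:** state that acuity and quality-of-life comparisons are among residents alive at that visit, with deaths by arm shown beside them. This also conditions on survival, but says so openly and keeps living residents who missed a visit. Call the per-protocol sample a completer sample.
- **Cost-effectiveness analysis:** set EQ-5D utility to 0 from death when QALYs are computed.
- **Retention and withdrawal:** record the date of death with the withdrawal reason.
- **Falls:** define one quantity, a rate, with time at risk as offset.

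The cost is small: analysis wording and one recorded date. Planned power is not reduced, because the enrolment figure already allows for the loss: 395 × 0.75 × 0.90 = 266.6, against the 266 required.
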